### Interventions

Each participant will undergo the first stage of data collection, the pre-test (T0), which will take place one day before the treatment period begins. This stage will consist of the administration of the four assessment instruments. Additionally, on this same day, participants assigned to the GE4 and GE5 groups will experience the interventions to familiarize themselves with how they will be conducted throughout the treatment.

The next stage involves the actual intervention. Regardless of the allocated group, all participants will undergo 10 treatment sessions, with each session lasting approximately 60 minutes. The entire study process will span a period of two weeks, with a two-day interval in the middle [27].

It is important to note that the activities to be imagined, observed, and executed during the interventions will be pre-selected by the therapist based on the participant’s preferences indicated through the COPM. The choice of activity will also depend on the dominance of the affected limb; if the dominant side is more affected, the activity will preferably be unilateral. However, if the more affected side is the participant’s non-dominant side, the activity will necessarily be bilateral. To ensure equal application of the interventions across all experimental groups, the techniques will be administered by the same therapist according to the following protocol:

#### 
Motor imagery (MI).

The activities will be narrated by the therapist during the intervention, guiding the participant - eyes closed and seated - to imagine executing the action from a first-person perspective, without the presence of motor symptoms and without performing any actual movement. To facilitate imagination, the participant may hold or grasp a real object related to the activity being imagined, either before or during the imagery, serving as a sensory stimulus for motivation. At the end of each imagined activity, the therapist will ask the participant whether they were able to imagine themselves performing the requested activity without motor symptoms. Each imagery session will last approximately 2 minutes.

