### Eligibility criteria

#### Inclusion criteria.

Have a diagnosis of PD and be at stages 1–3 on the Hoehn and Yahr scale [18]; be at least 20 years old; be on stable medication; achieve a score higher than 23 on the Montreal Cognitive Assessment (MoCA) [19]; score a minimum of 20 points on the Kinesthetic and Visual Imagery Questionnaire (KVIQ-10) [20,21]; exhibit motor impairment in the dominant UL, with scores above average according to manual dominance and sex in the 9-Hole Peg Test (9HPT) [22]; and have signed the Informed Consent Form.

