**Fig 2 pone.0315148.g002:**
[figure not shown]
Flowchart of participant distribution throughout each stage of the study. AO, action observation; BMI, brain machine interface; AE, action execution; EG, experimental group; MI, motor imagery.

Allocation will be carried out by a blinded investigator who will not be involved in the intervention. The randomization process will be carried out with a 1:1 allocation ratio through the website randomizer.com. It will not be possible to blind the participants and researchers who will carry out the training. However, the study will be blinded to the researchers for results and statistical analysis. This is a single-blind study, as the therapists (physical and occupational therapists) conducting the interventions will be different from those responsible for administering the assessment tools during data collection phases. Additionally, the blinding of data analysis will be ensured.

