### Data collection

The following instruments will be used for pre-intervention (T0) and post-intervention (T1) assessments. The Test d’Évaluation des Membres Supérieurs de Personnes Âgées (TEMPA) will be employed to evaluate limitations of the UL through tasks that simulate activities of daily living [23]. The final score of the test, which can reach up to 186 points, corresponds to the sum of the functional score, encompassing unilateral and bilateral tasks (totaling up to 36 points), and the task analysis score, which assesses five areas of sensory and motor skills in the UL (totaling up to 150 points). In this study, unilateral tasks will be performed using the more affected UL. For better interpretation, especially in task analysis, sessions will be recorded for subsequent analysis.

To assess fine manual motor performance, the 9-Hole Peg Test (9HPT) will be administered, considering the average times based on sex and manual dominance: for men, 21.1 seconds for the dominant hand and 22.3 seconds for the non-dominant hand; for women, 19.9 seconds for the dominant hand and 21.4 seconds for the non-dominant hand [22]. This instrument will be used as a screening tool, and data from included participants will be analyzed in the final results.

To evaluate motor disturbances in PD, the Unified Parkinson’s Disease Rating Scale - part III (UPDRS-III) will be utilized, which involves motor assessment [24], excluding items related to facial symptoms or those corresponding to motor symptoms in the lower limbs. The maximum score is 32 points, with higher scores indicating worse symptoms.

Cognitive functions will be assessed using the Parkinson´s disease -Cognitive Rating Scale (PD-CRS), which encompasses nine functions: sustained attention, working memory, immediate and delayed verbal memory recall, alternating verbal fluency, action verbal fluency, spontaneous clock drawing, visual confrontation naming, and clock drawing copying. The total score for the PD-CRS is 134 points [25].

The Canadian Occupational Performance Measure (COPM) is a semi-structured interview that identifies problem activities in the areas of self-care, productivity, and leisure. For this study, participants will choose up to five problem activities, rating them from 1 to 10 based on their performance and satisfaction [26]. In cases of motor symptoms in the non-dominant UL, participants will be instructed to select problem activities that involve more bimanual actions.

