### Statistical analysis

The results of qualitative variables will be expressed as absolute and relative frequency. Symmetric quantitative variables will be presented as mean and standard deviation, and asymmetric ones as median and interquartile range [P25 - P75]. The normality of the data will be checked using the Shapiro-Wilk test. Group characteristics will be compared using the Chi-square test, ANOVA, and/or false discovery rate (FDR) for the multiple comparisons between the 5 groups.

a) A mixed repeated-measures ANOVA will be used, or, in the absence of normality and/or in the presence of missing data, generalized estimating equations (GEE) models will be applied to assess the main effects of group and time, and the group*time interaction, with an unstructured correlation matrix. The goodness of fit will be assessed using the Quasi-Likelihood under Independence Model Criterion (QIC). The best-fitting distribution for the data (normal or gamma) will be evaluated using the AIC criterion, with identity or logarithmic link functions, respectively. Sidak’s test will be used for multiple comparisons. The results will be presented as means and 95% confidence intervals (CI). Analyses will be conducted using SPSS software (IBM SPSS Statistics for Windows, Version 25.0. Armonk, NY: IBM Corp.). The significance level will be set at 0.05.

### 
Trial status

Participant recruitment began in February 2023. Data collection and data analysis are expected end by September 2026.

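### The primary TEMPA model leaves out a baseline factor that the protocol itself uses to set the tested hand and the training type; adding it by time is a cheap gain in precision, not the repair of a bias

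*Protocol article*

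**What the plan says.** One baseline attribute, whether the more affected upper limb is the dominant one, appears in several rules of the protocol article.

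- Outcome measurement (Data collection): "In this study, unilateral tasks will be performed using the more affected UL". The tested hand is therefore dominant for some participants and non-dominant for others.
- Training content (Interventions): "The choice of activity will also depend on the dominance of the affected limb". The rule is that "if the dominant side is more affected, the activity will preferably be unilateral", whereas "if the more affected side is the participant’s non-dominant side, the activity will necessarily be bilateral".
- Choice of activities (Data collection): "In cases of motor symptoms in the non-dominant UL, participants will be instructed to select problem activities that involve more bimanual actions". These COPM choices feed the activities that are trained.
- Eligibility (Inclusion criteria): participants must "exhibit motor impairment in the dominant UL, with scores above average according to manual dominance and sex" on the 9HPT. This requires impairment of the dominant limb but does not require that limb to be the more affected one.

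On allocation (Randomization, allocation and blinding): "The randomization process will be carried out with a 1:1 allocation ratio through the website randomizer.com". No stratification factor is named. On analysis (Statistical analysis), a mixed repeated-measures ANOVA or GEE will be used "to assess the main effects of group and time, and the group*time interaction". No covariate is named. The Sample size section bases the 95 participants on the time-by-intervention interaction for TEMPA.

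**The concern.** The protocol separates participants into two kinds by a fact known before allocation. One kind trains mainly on unilateral tasks and is tested on unilateral TEMPA tasks with the dominant hand. The other trains on bilateral tasks and is tested on the unilateral TEMPA tasks with the non-dominant hand. The match between what is trained and what is tested differs between the two, so the amount of TEMPA change may differ too.

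If it does, a model with only group, time and group*time counts that difference as unexplained variation in change. The interaction test is then less sensitive than it could be, in a five-arm trial planned for 80% power. With 16 to 19 participants per arm, the mix of the two kinds will also vary between arms by chance, which makes individual arm contrasts noisier.

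**Working it through.** **1. The plan's own sample size.** Inputs from the Sample size section: f = 0.2, five groups, two assessments, alpha 0.05, power 80%, 19% attrition margin. The T0-T1 correlation is not stated; 0.5 is assumed. For the group*time test, lambda = f² × N × 2/(1 − rho), with 4 and N − 5 degrees of freedom. At N = 80, lambda = 0.04 × 80 × 2/0.5 = 12.8 with 4 and 75 df, and power is 80.3%. N = 80 is the smallest number that reaches 80%. Then 80 × 1.19 = 95.2, which matches the stated 95. Other correlations do not reproduce it: before attrition, N would be 155 at 0, 110 at 0.3, 65 at 0.6 and 35 at 0.8.

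**2. What can and cannot affect the test.** With two assessments, the mixed-ANOVA interaction test is a comparison of within-person change. A stable difference in TEMPA level between dominant and non-dominant hands cancels. Simulation with a level difference of 1 SD left the variance of change as it was (0.99 in both cases). Only a different amount of change matters: differences of 0.5 and 1.0 SD raised the variance of change to 1.05 and 1.24. The type I error of the unadjusted test stayed between 0.050 and 0.052 throughout.

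**3. Power with the factor by time added.** Let p be the share of participants whose non-dominant side is more affected, and g the difference in mean change between strata, in SD of change. At correlation 0.5 the variance of change is 2 × (1 − 0.5) = 1 in units of the score variance, so the two SDs coincide. The share of change variance explained is R² = p(1 − p)g². Lambda becomes 12.8/(1 − R²), with 4 and 74 df. The protocol gives neither p nor g, so a range is shown.

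| p | Power, g = 0.5 | Power, g = 0.8 |
|---|---|---|
| 10% | 81.3% (R² = 0.0225) | 82.9% (R² = 0.0576) |
| 20% | 82.1% (R² = 0.04) | 84.9% (R² = 0.1024) |
| 30% | 82.6% (R² = 0.0525) | 86.3% (R² = 0.1344) |
| 50% | 83.1% (R² = 0.0625) | 87.4% (R² = 0.16) |

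If g = 0, one degree of freedom is lost and power goes from 80.31% to 80.27%.

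**4. Chance imbalance between arms, without stratification, 19 per arm.** The binomial probability that the highest and lowest of the five arms differ by at least 30 percentage points in p is 38% at p = 50%, 28% at 30%, 16% at 20% and 2% at 10%. That is the extreme of five arms. For one given pair at p = 50%, the SD of the gap is sqrt(2 × 0.25/19) = 0.162, and the mean absolute gap is about 0.80 × 0.162 = 0.13, or 13 points. With g = 0.5 this moves the pairwise difference in change by 0.5 × 0.13 = 0.065 SD, against a standard error of sqrt(2/19) = 0.32 SD.

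**The case against.** The case against has considerable force.

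- **No passage shows that change differs by side.** The rules fix the tested hand and the preferred activity; they do not say that one kind of participant improves more. A reader might infer that the strata must differ in TEMPA change because of these rules. The documents do not support that. It is plausible and no more, and the 0.5 and 0.8 SD values are assumptions.
- **The strata overlap.** Unilateral training is only a preference, the article's medication example adapts a bilateral activity to dominant-side symptoms, and TEMPA also contains bilateral tasks. This argues for a modest effect of the factor.
- **Chance imbalance is not bias.** A reader might infer that unequal shares create a false arm difference. Under randomisation this variation is already reflected in the standard error, and the simulated type I error confirms it.
- **Eligibility may reduce the mix.** Requiring dominant-limb impairment may make low non-dominant shares more likely, and both imbalance and gain shrink with them. This stands, which is why shares down to 10% are shown. The protocol does write explicit rules for the non-dominant case, so it expects such participants.
- **There is no shortfall against the plan.** The effect size is standardised on total variability, so stratum variance is already inside the 80% target. This also stands.
- **An unseen SAP may name covariates.** It may. But the article does state the model terms, the correlation structure, the link functions and the multiplicity test, and the model as stated can be improved at almost no cost.

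**Conclusion.** The point holds as an optional efficiency improvement, not as an error in the design. Dominance of the more affected limb is known at baseline, is used by the protocol to set both the tested hand and the training type, and is absent from the stated primary model. If TEMPA change differs by this factor, precision is lost. Under the assumptions above (80 evaluable, correlation 0.5, non-dominant share 10% to 50%) the recoverable power is 1.0 to 2.8 percentage points for a 0.5 SD difference (81.3 − 80.3 to 83.1 − 80.3) and 2.6 to 7.1 points for 0.8 SD (82.9 − 80.3 to 87.4 − 80.3). If change does not differ, nothing is gained and 0.04 of a point is lost. A reader might go further and conclude that the primary comparison is confounded or the trial underpowered; neither follows, because allocation is random, type I error is unaffected and the stated sample size reproduces without the factor.

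**What to change.** Before analysis, and without reference to outcome data by arm, prespecify a two-level baseline factor: more affected side dominant or non-dominant. In the primary TEMPA model, add this factor and its interaction with time. The factor without the time interaction would change nothing in the T0-T1 group*time test. Alternatively, analyse T1 adjusted for T0, where the factor itself is enough.

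The cost is one line in the Statistical analysis section and one degree of freedom in the test of change. The protocol's own testing and training rules already require the side to be determined for every participant. The line should be fixed before results are seen, since added later it would be a post hoc choice. Stratifying any remaining allocation on the same factor is possible but not needed for the gain described here.

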#### MI via brain-machine interface (BMI).

The Neurobots equipment will be utilized (Exobots System Software: 1.10.0, Exobots Firmware version 2, EEG Firmware version 1, Neurobots, Pernambuco, Brazil). On the first day, the participant will be registered in the software system, and the therapist will provide a detailed explanation of the intervention, followed by a 2-minute training session with the Exobots system to ensure adequate understanding.

During the intervention, the participant will sit and wear a cap adjusted to their head circumference, containing EEG signal acquisition electrodes in the regions FC3, C3, CP3, FC4, C4, and CP4 (Fig 3). The electrode positioning will follow the international 10–10 EEG mapping standard. To ensure proper neural signal capture and low transmission impedance, the electrodes will be filled with conductive gel [28].

**Fig 3 pone.0315148.g003:**
[figure not shown]
BMI equipment system.

An exoskeleton will be attached to the more affected UL using Velcro straps on the forearm (1), wrist (1), and fingers (5). The participant will be instructed to keep their eyes closed, with their arm in flexion and abduction, elbow flexed at 90°, forearm pronated, wrist in a neutral position, and the hand with the exoskeleton resting on a cushion.

Each of the 10 intervention sessions will consist of 10 exercises with 5 repetitions (including the blocks “relax,” “prepare,” “think,” and “move”), with the 5 chosen tasks imagined twice. Each exercise will last 2 minutes, with a 30-second break between them for the participant to rest. The approximate duration of this stage will be 30 minutes. During each repetition, the participant will listen to four audio commands from the software system: “relax,” “prepare,” “think,” and “move.” When hearing “Relax”, the participant should think of nothing; during “Prepare” and “Think”, the participant will imagine the action, and during “Move”, the exoskeleton will automatically open and close the participant’s hand.

In the “relax” block, the software will quantitatively display this state on the computer screen through a feedback bar, indicating the absence of thought (a clear mind). In the “prepare” and “think” blocks, if the participant can maintain thought for at least 3 seconds (the established time window to avoid false positives) and achieve a score of 70 points (the minimum threshold shown on the feedback bar), the exoskeleton will move (opening and closing the participant’s hand), indicating that the system has detected continuous activation in the primary motor cortex, premotor cortex, or primary somatosensory cortex.

At the end of each exercise, performance will be verified through a graph provided by the system, displaying the score of the achieved degree of imagined movement alongside the most activated brain areas mentioned earlier. Upon completing the 10 intervention sessions, the system will display a graph showing the average degree of imagined movement for each session.

At the beginning of each session, it will be checked whether all 6 electrodes are active and if they detect any noise (wet air, metal objects, electronic devices, strong muscle contractions) that could interfere with the capture of the alpha wave signals in the brain. The manufacturer has established a 70% reduction (i.e., 70 points) in low-frequency activation (8–32 Hz), known as event-related desynchronization (ERD), as the activation threshold, an intermediate value between the observed percentage ranges [29].

#### Action observation (AO).

Participants will watch previously recorded videos by the therapist, in healthy conditions, from first and/or third-person perspectives, featuring front or side views that demonstrate the execution of activities. The AO will be conducted while seated, and the recorded videos will not be narrated and will be displayed on a computer screen. During the AO, participants will be asked to focus their attention on the details of the movements of the UL without making any movements themselves. Each observation session will last approximately 2 minutes.

#### Action execution (AE).

Participants will be instructed to perform the activities as imagined and observed, which can be done while seated or standing. They will be encouraged to execute the activities as they are able, with some activities prompting them to perform as quickly as possible or to alternate hand dominance based on motor symptom manifestation, especially in unilateral activities. Each execution session will also last approximately 2 minutes.

Below are presented the applicability sequences of each intervention group according to their respective approaches (Fig 4).

**Fig 4 pone.0315148.g004:**
[figure not shown]
Sequence of applicability of interventions. AO, action observation; BMI, brain machine interface; AE, action execution; EG, experimental group; MI, motor imagery.

During the intervention sessions, the difficulty of tasks may be adjusted as the participant progresses in execution, by altering the objects used in the activities, such as sizes, weights, resistances, and different shapes, to change the types of grips and pinches, as well as the range of motion, in addition to being prompted to perform as quickly as possible to stimulate movement speed. It is crucial that the environment is free from distractions to promote concentration during the sessions. Additionally, to ensure proper EEG recording, participants will be advised not to attend sessions with wet hair.

After the intervention period, each participant will undergo the second data collection phase, the post-test (T1), which will take place the day after completing the 10 intervention sessions. This phase will involve the administration of the same four evaluation instruments applied at T0, along with the 9HPT. On this day, participants will also be reminded of the third data collection phase, the follow-up (T2), scheduled to occur four weeks after the conclusion of the interventions. In the follow-up, participants will receive a call and will again respond to the COPM, reporting their satisfaction and performance regarding the problem activities, as well as completing a questionnaire on their perception of the severity of motor and cognitive functions (S1 Graphycal abstract).

Below are some sequences of images as examples of activities recorded on video for the AO. Three activities will be described, each involving an area of occupational performance: self-care, productivity, and leisure, detailed with technical descriptions of the executed movements and a narrative manner involving verbal commands for MI. Here are the examples:

The activity of organizing weekly medication (Fig 5) is a personal care activity, categorized under self-care according to the COPM, and involves various actions. We can choose only the action of holding the medication bottle with one hand and opening the cap with the other, unscrewing it. Another option is to select different medications, such as varying sizes and colors of tablets, to organize them into different days of the week, also stimulating cognitive functions. Therefore, we note that even though it is a bilateral activity, if the participant exhibits motor symptoms on the dominant side, the therapist will encourage the use of the dominant side to perform the actions of the activity, such as opening and closing the compartment lids, opening and closing the bottle cap, and holding the tablets. If the participant exhibits motor symptoms on the non-dominant side, the therapist will encourage the use of the contralateral side for the actions.

